### 8.1.1 Study Endpoints

#### Primary Endpoint:

Incidence of Grade 2 or higher Adverse Events deemed related to study product, graded according to the *Division of AIDS (DAIDS) Table for Grading the Severity of Adult and Pediatric Adverse Events, Version 2.0, Nov 2014* (Reference 39), and the Female Genital Grading Table for Use in Microbicide Studies (Addendum 1 to the DAIDS Table for Grading Adult and Pediatric Adverse Events, Version 1.0, December 2004 [Clarification dated August 2009]), (see Reference 40). Safety will be assessed throughout the study by monitoring of adverse events, vital signs, physical examinations, and/or clinical laboratory values, and review of concomitant medications and procedures. The number of Grade 2 or higher AEs will be the primary endpoint, but all AEs will be reviewed by the PSRT and analyzed regardless of severity or relationship.

#### Secondary Endpoints

##### Pharmacokinetic (PK)

- Naked eye visual assessment during speculum exam of the degree of film dissolution at 1, 4, and 24 hours after dosing
- Concentrations of MB66 antibodies in vaginal fluid sampled with Tear Flo (filter paper) wicks, and measured by ELISA
- Concentrations of MB66 antibodies in serum by ELISA

#### Exploratory Endpoints:

##### Ex vivo antiviral effect

- Assays of the ex vivo viral neutralization of HIV-1 and HSV-2 in cervicovaginal lavage fluid after MB66 dosing

#### Cervicovaginal microbial environment

- Vaginal pH
- Nugent score on Gram stained vaginal smears
- Vaginal microbiome assessment by polymerase chain reaction (PCR) for bacterial ribosomal DNA (samples stored for later analysis)
- Levels of immune mediators in cervicovaginal lavage fluid measured by Luminex and ELISA immunoassays

#### Immune modulators

- Assays of cytokines and other soluble immune mediators in CVL

#### Acceptability

- Determine acceptability of MB66 film by audio computer administered structured interview after 7 days of MB66 or placebo film.

## **8.2 DESCRIPTION OF STUDY POPULATION**

The study population will consist of healthy, low risk HIV-uninfected women who meet the criteria outlined in Sections [9.2](#) and [9.3](#).

## **8.3 TIME TO COMPLETE ACCRUAL**

Accrual is expected to be completed in approximately 12 months, with study completion in approximately 14 months.

## **8.4 STUDY GROUPS**

### **8.4.1 Segment A:**

Enrollment of 8 evaluable participants:

- Segment A participants: 1 MB66 film

### **8.4.2 Segment B:**

Randomization will be 1:1 amongst the two groups of 15 evaluable participants each:

- Segment B Study Arm 1: 1 MB66 film
- Segment B Study Arm 2: 1 Vehicle control placebo film

## **8.5 EXPECTED DURATION OF PARTICIPATION**

The duration of study participation per woman is expected to be approximately 5-9 weeks, including the screening period. Participation from enrollment to Exit Visit is 1 week for Segment A and 2 weeks for Segment B, plus an additional 2 weeks of post exit mandated condom use.

## **8.6 STUDY SITE**

The study will be conducted at a single study site: The Miriam Hospital, Providence, RI.

# **9. STUDY POPULATION**

## **9.1 SELECTION OF STUDY POPULATION**

The inclusion and exclusion criteria in this section will be used to ensure the appropriate selection of study participants.

Once a participant is enrolled, the study site will make every effort to retain her in follow-up to minimize possible bias associated with loss-to-follow-up (see Section 9.6). Participants may withdraw from the study at any time. No justification for such a decision is required. Participants must also be withdrawn from the study if the Investigator considers it in the best interest of the participant. The date and reasons for study withdrawal must be recorded in the case report form (CRF) and in the participant's study source documents. If possible, all final study assessments and procedures, such as a complete, final examination, should be performed on all participants who choose to withdraw or are withdrawn from the study. Whether due to loss of follow-up or inability to use study product, participants who are non-evaluable (see Section 14.2) will be replaced.

## **9.2 INCLUSION CRITERIA**

Women must meet all of the following criteria to be eligible for inclusion in the study:

- 1) Age 18 through 45 years (inclusive) at screening
- 2) Able and willing to provide written informed consent to be screened for and enrolled in the study
- 3) Able and willing to provide adequate locator information at screening
- 4) HIV-uninfected based on testing performed by study staff at screening (per algorithm in [Appendix 2](#))
- 5) In general good health as determined by the site clinician
- 6) Agree to abstain from any vaginal insertions, including products, douches, devices such as sex toys, or penile or oral intercourse from 5 days prior to Visit 2 (Enrollment Visit) until

the final Study Visit (one week after last dose of study film). Only tampons during menses and clinically indicated speculum exams are allowed.

- 7) Agree to use condoms provided by the study staff from one week after last use of study film until three weeks after last use of study film
- 8) Willingness to undergo all study-related assessments and follow all study-related procedures
- 9) Be currently using an effective method of contraception at enrollment (used continuously and with good compliance for the past 60 days as determined by participant self-report) with plans to continue use throughout the study period. Acceptable methods include any hormonal method (except vaginal ring); intrauterine device (IUD) inserted at least 90 days prior to enrollment; female sterilization; abstinent from sexual activity with male partner for the past 60 days; sexual activity with vasectomized partner; engages in sex exclusively with women.
- 10) For participants 21 and older, a Pap result in the 36 calendar months prior to the Enrollment Visit consistent with Grade 0 according to the Female Genital Grading Table for Use in Microbicide Studies Addendum 1 to the DAIDS Table for Grading Adult and Pediatric Adverse Events, (see Reference 40) satisfactory evaluation with no treatment required of non-Grade 0 Pap result per American Society for Colposcopy and Cervical Pathology (ASCCP) guidelines or per local standard of care, within the last 36 calendar months prior to enrollment.  
  
*Note: For participants aged 18-21, a Grade-0 or adequately evaluated abnormal Pap smear is not required as the American Society for Colposcopy and Cervical Pathology recommends initiating screening at age 21.*
- 11) At screening and enrollment, agrees not to participate in other research studies involving drugs, medical devices, or vaginal products while enrolled in this trial

### **9.3 EXCLUSION CRITERIA**

Women who meet any of the following criteria by participant report will be excluded from the study. Of note, the study is limited to pre-menopausal women with an intact uterus because the mucosal immune environment differs substantially between pre- and post-menopausal women. Therefore, inclusion of post-menopausal women would introduce heterogeneity into the population.

- 1) Menopausal at screening (as defined as amenorrhea or irregular periods for one year or more without an alternative etiology)
- 2) Hysterectomy
- 3) Known adverse reaction to any of the study products (ever)
- 4) Known adverse reaction to latex (ever)
- 5) Non-therapeutic injection drug use in the 12 months prior to screening

- 6) Surgical procedure involving the pelvis in the 90 days prior to screening (includes dilation and curettage or evacuation, and cryosurgery; does not include cervical biopsy for evaluation of an abnormal pap smear or IUD placement)
- 7) Participation in a drug, spermicide and/or microbicide study in the 30 days prior to screening or anticipated participation in an investigational drug study in the next 8 weeks
- 8) Pregnancy within 90 days prior to screening
- 9) Lactating
- 10) Use of a diaphragm, NuvaRing, or spermicide for contraception
- 11) As determined by the PI, a degree of menstrual cycle irregularity that would make it difficult to schedule follow up visits without interruption by menses
- 12) Active sexually transmitted infection or documented treatment of sexually transmitted infections in the last 6 months, including, but not limited to: chlamydia, gonorrhea, syphilis, trichomonas, cervicitis or pelvic inflammatory disease, or currently active HSV lesions or other sores. (Participants seropositive for or with a history of HSV without current active lesions will not be excluded.)
- 13) Women who by history engage in condom-less intercourse with HIV-infected partners, or who exchange sex for money, shelter, or gifts, or who in the opinion of the investigators, may be at risk for HIV acquisition during the duration of the study
- 14) More than one sex partner within the past 3 months
- 15) Current sexual partner known by participant to be HIV seropositive
- 16) Current or planned use of pre-exposure prophylaxis against HIV infection
- 17) Currently active genital HSV lesions, or other genital tract epithelial disruption or inflammation
- 18) Current or episodic use of anti-herpes suppressive therapy
- 19) Urinary tract infection, symptomatic candidiasis, or symptomatic bacterial vaginosis within 14 days of enrollment, or currently residual symptoms thereof

*Note: women with these infections at screening can be enrolled after treatment and resolution of the infection.*

- 20) Antibiotic or antifungal therapy (vaginal or systemic) within 7 days of enrollment
- 21) Use of systemic immunomodulatory medications within 4 weeks of enrollment
- 22) Menses or other vaginal bleeding at the time of enrollment\* or expecting menses in the 10 days after enrollment (Segment A participants) or 16 days after enrollment (for Segment B participants)

*\*Note: for women with monthly cycles, every attempt will be made to enroll these participants in the first half of their menstrual cycle. Women who have vaginal bleeding at the scheduled Enrollment Visit may return at a different date to be re-examined and*

*possibly enrolled provided they are still within the screening window and meet all criteria.*

- 23) Lack of stable living conditions to allow reliable room temperature storage of study product (Segment B participants only)
- 24) At enrollment has any of the following laboratory abnormalities per the *Division of AIDS (DAIDS) Table for Grading the Severity of Adult and Pediatric Adverse Events, Version 2.0, Nov 2014* (Reference 39):
- Grade 1 or higher AST or ALT
  - Grade 1 or higher creatinine
  - Grade 2 or higher hemoglobin
  - Grade 1 or higher platelets

*Note: otherwise eligible participants with an exclusionary test may be re-tested once during the screening process.*

- 25) As determined by the Principal Investigator (PI), any subject who has any significant uncontrolled active or chronic cardiovascular, renal, liver, hematologic, neurologic, gastrointestinal, psychiatric, endocrine, respiratory, immunologic disorder or infectious disease, anticoagulation with warfarin or heparin; or any other condition that, in the opinion of the Investigator, would preclude provision of consent, make participation in the study unsafe, complicate interpretation of study outcome data, or otherwise interfere with achieving the study objectives.

#### **9.4 CO-ENROLLMENT CRITERIA**

As mentioned in Section 9.3 (Exclusion Criterion #7), participation is prohibited in any drug, spermicide and/or microbicide study in the 30 days prior to screening, as is anticipated participation (co-enrollment) in an investigational drug study in the 8 weeks following enrollment in the present trial.

#### **9.5 RECRUITMENT PROCESS**

Participants will be recruited from a variety of sources including the ambulatory clinic of The Miriam Hospital and the surrounding population. Participants will also be referred to the study from other local research projects, research registries, IRB approved advertisements, and other health and social service providers serving the target study population. Recruitment materials will be approved by the Miriam Hospital Institutional Review Board (IRB).

#### **9.6 PARTICIPANT RETENTION**

Once a participant is enrolled, the study site will make every effort to retain her in follow-up to minimize possible bias associated with loss-to-follow-up. The site will implement the following procedures to enhance retention:

- Thorough explanation of the study visit schedule and procedural requirements during the informed consent process and re-emphasis at each study visit
- Thorough explanation of the importance of all study groups to the overall success of the study
- Collection of detailed locator information at the study Screening Visit, and active review and updating of this information at each subsequent visit
- Use of appropriate and timely visit reminder mechanisms
- Immediate follow-up on missed visits

Participants may withdraw from the study at any time. No justification for such a decision is required. Participants must also be withdrawn from the study if the Investigator considers it in the best interest of the participant. The date and reasons for study withdrawal must be recorded in the case report form (CRF) and in the participant's study source documents. If possible, all final study assessments and procedures, such as a complete, final examination, should be performed on all participants who choose to withdraw or are withdrawn from the study.

The study site will use a participant tracking mechanism to facilitate visit scheduling and timely identification and follow-up on missed visits. Whether due to loss follow-up or inability to use study product, participants who are non-evaluable (see Section 14.2) will be replaced.

## 9.7 PLANNED SAMPLE SIZE

An estimated 43 study participants from a single study center at The Miriam Hospital, Providence, RI will be enrolled to reach 38 evaluable subjects.

## 10. STUDY PRODUCT

### 10.1 IDENTITY

|                                                                         |                                                                                                                                                        |
|-------------------------------------------------------------------------|--------------------------------------------------------------------------------------------------------------------------------------------------------|
| Biologic name:                                                   | VRC01-N monoclonal antibody
HSV8-N monoclonal antibody                                                                                              |
| Dosage form:                                                     | Vaginal film                                                                                                                                           |
| Strength:                                                        | 10 mg of each monoclonal antibody per film                                                                                                             |
| Contract Manufacturer
(Drug Substance and
Drug Product): | Kentucky Bioprocessing, Inc.
[name]
Owensboro, KY 43201
(Contract Manufacturer for Sponsor Leaf Bio, Inc.)                          |
| Proposed Indication(s)
or context of product
development | Topical anti-microbial agent used to reduce mucosal transmission of human immunodeficiency virus type 1 (HIV-1) and human herpes simplex virus (HSV-2) |

The study will test the safety of the MB66 film containing the monoclonal antibodies VRC01-N and HSV8-N in MB66 films containing a dose of 10 mg of each antibody in each film. In Segment A, the study clinician will administer a single dose of one MB66 film with a dose level of 10 mg of each antibody. Then in Study Segment B, dosing will escalate to seven daily doses of one MB66 film (10 mg of each antibody daily) tested against the vehicle control placebo.

## 10.2 REGIMEN

Segment A participant will receive the following regimen:

- 1 MB66 film

Segment B participants will be randomized to one of the following regimens:

- Study Arm 1: 1 MB66 film
- Study Arm 2: 1 vehicle control placebo film

Study films will be provided individually sealed in a lightproof foil laminate (Mylar) pouch. Packaged study film will be stored at 2-8 °C until dispensed and at room temperature once dispensed to Segment B participants.

**Table 4: Study Dose Regimen**

| Study Group      | Regimen                                                                                                      |
|------------------|--------------------------------------------------------------------------------------------------------------|
| Segment A |                                                                                                              |
| MB66 film        | Single dose of one MB66 film
(10 mg VRC01-N and 10 mg HSV8-N) (8 evaluable participants)                  |
| Segment B |                                                                                                              |
| MB66 film        | Seven daily doses of one MB66 film *
(10 mg VRC01-N and 10 mg HSV8-N per day) (15 evaluable participants) |
| Placebo film     | Seven daily doses of one placebo film * (15 evaluable participants)                                          |

\*The Visit 4 target date for Segment B is Day 7, though the window for the visit includes Day 8. Consequently, some participants will receive 8 daily doses, although every effort will be made to schedule participants for Day 7 if feasible, to limit the variation in dosing.

## 10.3 ADMINISTRATION

A study clinician will manually insert the MB66 film in the clinic for Segment A participants, and Segment B participants will self-administer their first dose of study film in clinic in the presence of the study clinician (to assure themselves and study staff of their ability to insert the film), and then self-administer doses 2-7 at home. Segment B participants will take home their remaining doses in a vial capped with a Medication Event Monitoring System (MEMS) cap, to provide objective data about adherence with and timing of at home dosing, (each opening of the MEMS cap will be electronically recorded for time and date, with data downloaded at Visit 4). An extra dose of study film will be available for each Segment A participant in case of an

initially unsuccessful insertion, and three extra doses provided for each Segment B participant in case of unsuccessful insertion in clinic, at home, or for the possibility of delaying Visit 4 to Day 8 instead of Day 7. *(While the intended duration of exposure for Segment B participants is 7 days, participants who are only able to reschedule Visit 4 on Day 8 post MB66 administration will be allowed to do so. For that group, the total dosing will be 8 days rather than 7. Every effort will be made to bring participants back on Day 7 so as to minimize variation in product exposure. Participants will only be enrolled if they indicate their availability to return on Day 7, but if a scheduling conflict should arise post enrollment, they will be allowed to return to the clinic for Visit 4 on Day 8 after administering an additional dose of film on day 7.)*

For Segment A participants the study will be open label (unmasked). For Segment B, the film identity (active or placebo) will be randomly assigned and assignment will be single blinded (study film identity will be masked to the participants) Reliable blinding of study staff will not be feasible due to the non-identical degree of film translucency of the active and placebo films.

The film is folded once and draped over the index or middle finger of the dominant hand, and advanced into the vagina, initially supported by an adjacent finger and thumb. A commercially available vaginal film (VCF contraceptive film) with size and properties very similar to MB66 film will be used to demonstrate film folding and finger placement, (but will not be placed in the participant's vagina). Detailed training (video instruction, one-on-one instruction, and hands-on training with insertion of VCF film into pelvic models) will be provided so that both the study staff and participants are confident in women's ability to insert the film to full depth within the vagina. The video is the VCF contraceptive film video and shows how to open the packaging, fold the film, position it on a finger, and then insert it into a transparent pelvic model (the video may be viewed at: <http://www.vcfcontraceptive.com/howdoesvcfwork.html>). As part of the adherence and product use counseling, Segment B participants will be reminded to wash and dry their hands before and after administration, to avoid use of lotions after washing, and to avoid insertion of other vaginal products. They will receive instruction on the MEMS cap system, which will provide objective data about adherence with at home dosing, (each opening of the MEMS cap is electronically recorded for time and date). Vials of appropriate size will be provided to allow storage and removal of the stacked film pouches.

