## **10.6 STUDY PRODUCT SUPPLY AND ACCOUNTABILITY**

LeafBio, Inc. is the IND holder for MB66 film and will take responsibility to ensure that its contract manufacturer, (Kentucky Bioprocessing, Inc.) provides the appropriately packaged and labeled study product to the Miriam Hospital Research Pharmacy. All study products will be stored in and available to the study staff through the Research Pharmacy.

The Miriam Hospital research pharmacist will maintain complete accountability records of all study products received for this protocol and dispensed to participants. These records will not be available to other members of the research staff. Additional documentation will be required for study film returns, destruction (if applicable) and other related issues as outlined in instructions for DAIDS clinical trials.

Film will be stored at 2-8° C in the Miriam Research Pharmacy until dispensed, and at room temperature in participant's homes during 6 days of at-home dosing. Participants will be instructed to return any films not used at home to study staff, and returned to the pharmacy for quarantined storage until study completion. All returned or otherwise unused film will be destroyed by the Research Pharmacy after study completion.

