## **10.8 ASSESSMENT OF PARTICIPANT STUDY PRODUCT ADHERENCE**

Dosing of Segment A participants will be performed by a study clinician. The first dose for Segment B will be placed by the participant in the clinic in the presence of a study clinician. Doses 2-7 for Segment B participants will be administered by participants at home, and adherence will be monitored by the use of MEMS cap devices (see Section 10.3 and 11.1.2.4). MEMS cap data will be used to determine which Segment B participants are sufficiently adherent to be evaluable (see Section 14.2) and will be included in the mITT (per protocol) analysis (see Section 14.7.5).

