#### 11.1.2.4 Segment B, Visit 3: Follow-up Day 1 with PK Sampling

This visit will assess safety endpoints and adverse events, obtain vaginal Tear Flo samples to determine study Mab concentrations and vaginal distribution of the study MABs, and obtain a blood sample to determine the level of systemic absorption of the study MABs, and perform other testing as outlined in [Table 12](#). All vaginal sampling (swabs, Tear Flo strips, and CVL) will be performed via speculum. The participant will be given eight doses (thus including two extra

doses) of the study product to be administered at home within a container capped with a MEMS cap to provide an electronic record of opening for disbursing each dose. Testing of the proper functioning of the MEMS cap device will be performed, and instructions for its use will be reviewed, including cautioning against “curiosity openings”, and cautioning against removal of more than one film at a time. Participants will be reminded of the need for storage at controlled room temperature, and to avoid high temperature exposures outside the home, for example leaving the films in a vehicle. Instructions on film insertion will be reiterated, and participants will be asked if they have questions about film insertion and if they wish to do further training with the pelvic models.

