## 14.2 SAMPLE SIZE AND ACCRUAL

The primary aim of the study is to assess the local and systemic safety of one and seven day exposures to MB66. The primary endpoint is the proportion of participants who experience a Grade 2 or higher adverse event (AE) deemed related to study product. (The proposed total sample size is N=38 evaluable participants divided into Segment A (with n = 8 evaluable), and Segment B (with two arms, a MB66 arm and a placebo film arm, each with n = 15 evaluable). Evaluable participants (evaluable for the primary endpoint) in Segment A will be defined as participants who complete the Screening and Enrollment Visits and return for Visit 3. Evaluable participants in Segment B will be defined as participants who complete the Screening and Enrollment Visits and return for Visit 4 and use study product for at least 5 of the previous 7 days including the day before presentation (as assessed with MEMS cap data). Non-evaluable participants will be replaced, however, their data relevant to endpoints other than the primary endpoint will be preserved and used in tabulation and analysis of secondary and exploratory endpoints. In addition, if a participant becomes non-evaluable prior to the predefined visits described above, but experiences an AE during the time they were on study, their data will be included in the primary analyses as well. Based on previous studies of vaginal products conducted at the study site, the accrual of 38 evaluable subjects with normal reproductive tracts is expected to require the screening of approximately 70 participants and the enrollment of approximately 43 participants. The target for retention will be approximately 90% of enrolled participants over the 7-14-day follow-up period. Therefore, it is anticipated that 23 women exposed to active study drug in all arms (8 during Segment A and 15 during Segment B) will be evaluable. [Table 16](#) calculates the probability of events in Segment A participants (n=8) and [Table 17](#) calculates the probability of events in Segment B participants (n=15).

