**Table 17: Exact Binomial probabilities for different scenarios for Segment B (n=15) for Study MB66-01**

| Event Rate | P
(No events   n=15) | P
(1 event   n=15) | P
(2 or more events   n=15) |
|-------------------|---------------------------------|-------------------------------|----------------------------------------|
| 1%                | 0.86                            | 0.13                          | 0.01                                   |
| 5%                | 0.46                            | 0.37                          | 0.17                                   |
| 10%               | 0.21                            | 0.34                          | 0.45                                   |
| 15%               | 0.09                            | 0.23                          | 0.62                                   |
| 20%               | 0.04                            | 0.13                          | 0.83                                   |
| 25%               | 0.0134                          | 0.067                         | 0.92                                   |
| 30%               | 0.005                           | 0.03                          | 0.965                                  |

The sample size for Segment A is large enough to rule out 50% Grade 2 or higher adverse rate with n=8 patients. With 8 participants in this segment a one-sided 95% Clopper-Pearson (exact) binomial confidence interval will have an upper limit of 47% if one out of eight women has a Grade 2 (or higher) adverse event (AE2) related to the study product. Furthermore, the sample size for Segment B was chosen to have an adequate sample size to rule out 30% grade 2 or higher adverse event rate for each of the groups. With 15 participants in an arm a one-sided 95% Clopper-Pearson (exact) binomial confidence interval will have an upper limit of 27.9% if one out of 15 women has an AE2 related to the study product.

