AE2's will be estimated for each group. The focus of these analyses will be to determine whether a 30% AE2 rate can be ruled out based on the data collected in the study. This will be shown if the upper bound of the 1-sided 95% Clopper Pearson (exact) binomial confidence interval is less than 30% which will occur if zero or one participant out of the 15 enrolled (in each arm) have an AE2. In addition, an exploratory comparison between the two groups in Segment B (active and vehicle) will be performed using a Fisher's Exact test to determine whether the number of participants with Grade 2 or higher AEs are different between groups. In addition to estimating the rate of Grade 2 (or higher) AE's in Segment B alone, estimates of combined Grade 2 or higher AEs rates can be derived by pooling the participants from Segment A and Segment B. In addition, Segment A participants (n=8) can be pooled with the participants from Segment B, allowing for Grade 2 or higher AEs estimates to be made using n=23 participants. One-sided 95% Clopper-Pearson (exact) binomial confidence intervals will be estimated for these AE2 rates. For the analyses with n=23 participants, the confidence intervals will have an upper bound of 29.4% if 2 (or fewer) participants have an Grade 2 or higher AEs. These analyses will provide supportive data to the primary endpoint analysis that is based on the Segment B (n=15) participants only. Additional detail of the statistical analyses will be provided in a separate statistical analysis plan (SAP), which will be prepared and signed off prior to completion of the study.

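### Segment B evaluability credits film use from MEMS cap openings alone, without checking them against the unused films handed back at Visit 4

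*Protocol*

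**What the plan says.** Protocol Section 14.2 makes a Segment B woman evaluable if she completes Screening and Enrollment, returns for Visit 4 and meets this usage condition: "use study product for at least 5 of the previous 7 days including the day before presentation (as assessed with MEMS cap data". The Protocol Summary (Section 5) gives the same rule, and Section 10.8 confirms the source: "MEMS cap data will be used to determine which Segment B participants are sufficiently adherent to be evaluable". Section 10.3 describes what the device captures: "each opening of the MEMS cap will be electronically recorded for time and date, with data downloaded at Visit 4".

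Section 14.7.5 makes the evaluable women the mITT group used for the primary analysis. Section 14.7.2 then judges each arm by whether the "upper bound of the 1-sided 95% Clopper Pearson (exact) binomial confidence interval is less than 30" per cent, "which will occur if zero or one participant out of the 15 enrolled (in each arm) have an AE2". The supporting figure in Section 14.2 is that the interval "will have an upper limit of 27.9% if one out of 15 women has an AE2 related to the study product".

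Eight films are dispensed in the capped vial on Day 1 for six planned home doses, so two are spare (Section 11.1.2.4, Table 12). Section 10.6 adds: "Participants will be instructed to return any films not used at home to study staff". Section 11.1.2.6 and Table 13 place that return at Visit 4. Section 11.1.2.4 has staff warn women against opening the vial out of curiosity, and the same instructions include "cautioning against removal of more than one film at a time". Nowhere is the number of films returned compared with the number of openings or brought into the evaluability rule.

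**The concern.** An opening does not show that a film was taken out. The protocol recognises this, because it counsels against idle openings, but counselling is its only remedy in the rule. The returned films are a direct check that reaches staff at the visit where the cap data are downloaded: a film handed back unused cannot have been used. Because the rule ignores it, a woman whose openings overstate her use is counted as having had at least 5 of 7 days' exposure. If she has no related Grade 2 or higher event, she adds an event-free unit to the denominator and so lowers the upper bound that decides whether 30% is ruled out. The error favours a conclusion of safety.

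**Working it through.** **1. The rule applied to one case.** Take Visit 4 on Day 7, so the previous 7 days are Days 0 to 6. A woman opens the vial once on each of Days 1 to 6 and hands back all 8 films.

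- Rule as written: 6 days with openings, at least 5, so evaluable.
- Films she can have used at home: at most 8 − 8 = 0. Her real use in the window is the one film inserted in clinic before the clinician on Day 0 (Section 10.3).

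Let R be the films returned, H the home days in the window with an opening, and D = 1 if Day 0 lies in the window and 0 otherwise. Each day of use consumes at least one film, so home days used cannot exceed 8 − R. A capped credit is

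credited days = D + min(H, 8 − R).

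- The woman above: 1 + min(6, 0) = 1, below 5, so not evaluable.
- Full use with Visit 4 on Day 7, spares returned (R = 2): 1 + min(6, 6) = 7.
- Full use with Visit 4 on Day 8 (window Days 1 to 7, D = 0, R = 1): 0 + min(7, 7) = 7.

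A failed insertion uses a spare and makes R smaller, which loosens the cap. The cap can therefore remove false credit but not earned credit.

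**2. The plan's own figure.** The one-sided 95% Clopper-Pearson upper limit for x events in n women is the 0.95 quantile of Beta(x + 1, n − x).

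- 1/15: 27.94%, matching the stated 27.9%.
- 2/15: 36.3%, so zero or one event is the correct cut-off for 30%.

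**3. Illustration.** Let k of the 15 be women whose credit is false. The protocol gives no value for k, so it is assumed. Discounting them, before any replacement:

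| k | n = 15 − k | Bound, 1 event | Bound, 0 events |
|---|---|---|---|
| 0 | 15 | 27.9% | 18.1% |
| 1 | 14 | 29.7% | 19.3% |
| 2 | 13 | 31.6% | 20.6% |
| 6 | 9 | 42.9% | 28.3% |
| 7 | 8 | 47.1% | 31.2% |

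With one event the bound crosses 30% at k = 2. With zero events it crosses at k = 7.

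**4. Chance of passing at a true rate of 30%.** This is P(X ≤ 1) = 0.7^n + n × 0.3 × 0.7^(n−1), if the k women carry no event risk.

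- n = 15: 0.0047 + 0.0305 = 3.5%.
- n = 13 (k = 2): 0.0097 + 0.0540 = 6.4%.

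No risk at all is an extreme assumption, given the Day 0 dose. For k = 2 the figure is 5.9% if such women carry one seventh of the risk and 4.9% if they carry half.

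**The case against.** Several points on the other side stand.

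- A reader might infer that such women are unexposed and event-free by construction. They are not. The first dose is witnessed, and a related Grade 2 or higher event after it counts. They are under-exposed.
- A reader might also infer that a pass at 1/15 would exist only because of them. That is not shown. Sections 9.1 and 14.2 replace non-evaluable women, so a corrected rule would bring the denominator back to 15, and one event would again give 27.9% unless a replacement had an event. The 1/14 and 1/13 bounds are not what the corrected design would yield.
- It is tempting to add that women who remove several films at one opening are wrongly failed, and to settle such cases from the Visit 4 interview. That would let site staff, whom Section 14.5 says cannot reliably be blinded, decide evaluability at the visit where they collect adverse events. Preferring objective openings to such a judgement is defensible.
- A return count misses films taken out and discarded, and the two spares make the cap loose.
- The Day 3-4 call, the Visit 4 interview and the 24-hour antibody sample (informative in the active arm only) are partial checks, and an ITT cohort is defined.

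What does not stand is the suggestion that this is only detail for the SAP, to which Section 14.7.2 defers further analysis. Evaluability is fixed in the protocol and operates during accrual, through replacement and the altered randomisation blocks of Section 14.6. None of the partial checks enters the rule.

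**Conclusion.** The point holds in a limited form. Segment B evaluability, and with it the primary denominator, rests on cap openings alone, while a more direct check that can only remove false credit is handed over at Visit 4 and left unused. No figure in the primary rule is miscalculated: 27.9% reproduces.

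The effect is modest and its size unknown. On the assumed counts, one misclassified woman in an arm changes nothing. Two would move a one-event bound above 30% before replacement, and a zero-event result would need about seven. The documents do not support saying that the trial's safety conclusion depends on this. They support a cheap tightening of the rule before evaluability is decided.

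**What to change.** In Sections 10.8 and 14.2:

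- Have the staff who receive the films at Visit 4 record the number of unused films returned. Pharmacy accountability records will not serve, because Section 10.6 withholds them from other research staff.
- Define days of use as the witnessed Day 0 dose, where it falls in the 7-day window, plus home days with a MEMS opening, capped at 8 minus films returned. Stating the Day 0 credit matters because the vial is dispensed only on Day 1, so MEMS cannot record that dose.
- Treat a woman who then falls below 5 days as non-evaluable and replace her under the existing rule. State that any adverse event she had still enters the primary analysis, as Section 14.2 provides for women who become non-evaluable earlier.
- Do not use interview history to decide evaluability.
- Report the AE2 upper bound under both the MEMS-only and the capped definitions.

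The cost is one recorded count per woman at Visit 4, a few lines of text and possibly a few more replacements. Films removed and discarded remain undetected. The cap does not show which opening was empty, so the day-before-visit condition still rests on the cap record.
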